# Comparing 2-Hz and 100-Hz Electroacupuncture for Postoperative Musculoskeletal Pain: Protocol for a 2 × 2 Prospective Randomized Crossover Trial

**DOI:** 10.2196/91706

**Published:** 2026-06-16

**Keywords:** electroacupuncture, chronic postsurgical pain, pulse rate variability, radial pulse tonometry, acupoint, crossover trial

## Abstract

**Background:**

Postoperative pain after musculoskeletal surgery impedes early rehabilitation and reduces quality of life. Electroacupuncture is used as an adjunct for analgesia, but the optimal stimulation frequency and short-term response trajectory have not been established.

**Objective:**

The aim of this study is to compare frequency-dependent relative analgesic responses to bilateral ST36 to SP9 electroacupuncture at 2 Hz and 100 Hz and generate effect size and variability estimates to inform future definitive trials.

**Methods:**

This single-center, frequency-masked, active-comparator, 2 × 2 prospective randomized crossover trial will enroll 30 adults (aged 19-80 years) experiencing pain (numerical rating scale [NRS] score≥4) after musculoskeletal surgery. Participants will undergo two 15-minute electroacupuncture sessions at bilateral ST36 to SP9 (2 Hz and 100 Hz) separated by a washout period of at least 7 days. Participants will not be informed of the assigned stimulation frequency or treatment sequence.

**Results:**

Participant recruitment began in September 2025, and data collection is expected to be completed by August 2026. Data analysis will begin after database finalization in late 2026, with primary findings submitted for publication in April 2027. The primary outcomes are baseline-adjusted changes in pain NRS scores at 15 minutes and 2 hours after each intervention. Secondary outcomes include pain NRS scores immediately after and at 1, 4, and 24 hours after electroacupuncture; pain location and quality; photoplethysmography-derived pulse rate variability, used as a surrogate for heart rate variability; radial pulse tonometry parameters; and wrist-worn activity metrics.

**Conclusions:**

This protocol describes an active-comparator crossover trial designed to estimate relative immediate and short-term analgesic responses to 2-Hz vs 100-Hz electroacupuncture and associated physiological measures in postoperative musculoskeletal pain. Because the trial does not include a sham, usual care, or no-additional-electroacupuncture control arm, it will not determine the absolute efficacy of electroacupuncture or separate specific effects from nonspecific contextual or placebo effects. Results from this trial will help optimize stimulation parameters and outcome assessments for larger, definitive efficacy trials.

**Trial Registration:**

Clinical Research Information Service KCT0011009; https://tinyurl.com/54phyep7

**International Registered Report Identifier (IRRID):**

DERR1-10.2196/91706

## Introduction

Musculoskeletal procedures such as total knee arthroplasty, spinal surgery, and total hip arthroplasty are becoming increasingly common with population aging. These procedures improve functional outcomes and reduce pain. However, postoperative pain often persists, and this can delay early mobilization and rehabilitation. Some patients develop chronic postsurgical pain [1-3]. Neuropathic components frequently coexist with and complicate pain control after spinal surgery [4]. Pharmacological strategies alone are insufficient for many patients, and current guidelines emphasize multimodal, multidisciplinary pain management [5-7]. Inadequate acute pain control after total knee arthroplasty can lead to chronic pain and long-term decrements in function and quality of life [8-10].

Electroacupuncture is a minimally invasive adjunctive analgesic option. Clinical trials and systematic reviews in arthroplasty populations suggest benefits in pain reduction, opioid sparing, and functional recovery [11,12]. Compared with other neuromodulation techniques such as transcutaneous or peripheral nerve stimulation, electroacupuncture is less invasive and easier to deploy at the bedside [13,14].

The evidence base for electroacupuncture after arthroplasty has expanded, but many crossover or repeated-exposure trials on postoperative pain have not clearly specified a washout period or formally assessed carryover effects [15,16]. The analgesic effect of a single acupuncture session may wane over tens of minutes to several days (approximately 30-72 hours) depending on the condition [17,18], whereas more invasive neuromodulation such as spinal cord stimulation can show residual effects for up to 5 days [19]. On the basis of this, our crossover trial adopts a conservative washout period of at least 7 days to minimize carryover.

The analgesic effects of electroacupuncture are frequency dependent. Low-frequency stimulation (2 Hz) preferentially elicits β-endorphin and enkephalin release, whereas high-frequency stimulation (100 Hz) engages dynorphin-mediated pathways. These findings suggest that the peptide systems are partially distinct [20]. Responsiveness varies across individuals, and intrinsic factors may contribute to this heterogeneity [21]. Procedure- and patient-specific factors also influence postoperative pain intensity [9,22]. Therefore, a 2 × 2 crossover design with intraindividual comparisons is well suited to compare the effects of 2-Hz and 100-Hz stimulation and control for interindividual variability.

The primary hypothesis of this study is that 2-Hz and 100-Hz electroacupuncture will produce different short-term analgesic responses, measured as baseline-adjusted changes in pain numerical rating scale (NRS) scores at 15 minutes and 2 hours after stimulation. This frequency-masked, active-comparator, 2 × 2 randomized crossover study aims to compare relative responses to bilateral ST36 to SP9 electroacupuncture at 2 Hz and 100 Hz.

## Methods

### Study Registration

The study has been registered with the Clinical Research Information Service under registration number KCT0011009.

### Patient and Public Involvement

Patients and/or the public were not involved in the design, conduct, reporting, or dissemination plans of this research.

### Study Design

This will be a single-center, frequency-masked, active-comparator, 2 × 2 prospective randomized crossover trial. Because no sham, usual care, or no-additional-electroacupuncture arm will be included, electroacupuncture administration itself is open label; however, participants will not be informed of the stimulation frequency applied at each visit or of the treatment sequence. Each participant will present for 2 treatment visits (visits 1 and 2) separated by a washout period of at least 7 days. This duration was selected as a conservative measure to minimize potential carryover of analgesic effects. Participants will be randomized (1:1) to 1 of 2 sequence groups: group 1 will receive mode A (2 Hz) followed by mode B (100 Hz), and group 2 will receive the reverse sequence (mode B followed by mode A). This design enables within-participant comparisons of immediate and short-term responses to the 2 frequencies while reducing interindividual variability (Figure 1). This protocol was prepared primarily with reference to the SPIRIT (Standard Protocol Items: Recommendations for Interventional Trials) 2025 guidelines for randomized controlled trial protocols [23]. Reporting elements specific to the crossover design were additionally supplemented with reference to the CONSORT (Consolidated Standards of Reporting Trials) extension for randomized crossover trials [24].

**Figure 1 figure1:**
[figure not shown]
Flowchart of the study design.

### Eligibility Criteria

The inclusion criteria will be as follows: (1) age of 19 to 80 years, (2) postoperative musculoskeletal pain with an NRS score of 4 or higher at enrollment, and (3) ability to complete questionnaires and provide written informed consent. The date and type of the index surgery, postoperative day at screening, and postoperative day at each treatment visit will be recorded.

The exclusion criteria will be as follows: (1) pain not attributable to the index surgery or underlying musculoskeletal condition, (2) pregnancy or breastfeeding, (3) having undergone acupuncture or electroacupuncture within 7 days before screening, (4) participation in another clinical trial within 1 month or scheduled surgery within 2 weeks, (5) severe phobia of acupuncture or electrical stimulation or known adverse reactions, (6) contraindications at the needling sites (eg, fresh incision or suture line, infection, severe edema due to deep vein thrombosis, or malignancy), (7) uncontrolled major neuropsychiatric disorders (eg, major depression, schizophrenia, and bipolar disorder), and (8) any condition that the investigators consider to preclude safe participation.

### Interventions

Electroacupuncture will be administered by a licensed doctor of Korean medicine with more than 5 years of clinical acupuncture experience after completion of study-specific protocol training. Electroacupuncture will be administered at bilateral ST36 (Zusanli) and SP9 (Yinlingquan) using sterile, disposable needles (0.20 × 30 mm) connected to a medical electroacupuncture stimulator. Needles will be inserted to a depth of 15 to 25 mm for ST36 and 10 to 20 mm for SP9, with minor adjustments permitted based on individual anatomy and clinical safety. If insertion depth differs from the predefined range for safety or clinical reasons, the reason will be recorded in the electronic case report form (eCRF). A single 15-minute continuous stimulation at the assigned frequency will be administered at each visit. The current intensity will be gradually increased to the lowest clearly perceptible level that remains comfortable and tolerable for each participant to standardize sensory engagement while ensuring tolerability. Achievement of the qi sensation will not be required for treatment completion. Needles will be removed immediately after completion of the 15-minute electrical stimulation. If a participant reports severe discomfort, pain, dizziness, vasovagal symptoms, bleeding, skin abnormalities, or any other adverse event (AE) or requests discontinuation, electrical stimulation will be stopped immediately, and the needles will be removed. Electroacupuncture will be administered in 2 modes: mode A (2-Hz electroacupuncture at bilateral ST36-SP9) and mode B (100-Hz electroacupuncture at bilateral ST36-SP9).

### Physiological Measurements and Activity Monitoring

Pulse rate variability (PRV) will be measured using the ubpulse T1 device (LAXTHA Inc), which is based on photoplethysmography. The device analyzes pulse-to-pulse intervals derived from photoplethysmography pulse waves; therefore, the outcome will be described as photoplethysmography-derived PRV, used as a surrogate for heart rate variability. A photoplethysmography clip sensor will be attached to the tip of the left index finger. For PRV measurement, after the photoplethysmography clip sensor is attached, an additional 2- to 3-minute stabilization period will be allowed before the 1-minute recording. After completion of the measurement, the sensor will be removed according to the software instructions. The collected signals will be analyzed using the manufacturer-provided software according to predefined artifact handling and analysis procedures.

Radial pulse tonometry will be standardized at the right radial artery. If movement occurs during radial pulse tonometry and data error is suspected, the measurement will be repeated. The activity device will be worn on the left wrist whenever feasible. The activity device will be attached immediately following the intervention and removed upon completion of the 2-hour in-clinic observation period.

Electroacupuncture, PRV, and radial pulse tonometry will be performed in the supine position whenever feasible. If the supine position is clinically contraindicated or intolerable for the participant, the sitting position will be permitted and documented in the eCRF. For each participant, the same position will be maintained for baseline and postintervention measurements whenever feasible. During PRV and radial pulse tonometry measurements, participants will be instructed to avoid talking, unnecessary movement, and posture changes. Wrist-worn activity monitoring is intended to record actual activity during the 2-hour in-clinic observation period; physiological measurements will not be performed during active movement. Participants will remain in a designated observation area; however, minimal movement will be permitted when required for safety or clinically appropriate reasons.

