### Schedule of Enrollment, Interventions, and Assessments

The participants will undergo screening and baseline assessments before randomization and electroacupuncture administration at 2 Hz or 100 Hz during visit 1. Pain NRS scores will be recorded immediately before the intervention and immediately after and at 15 minutes, 1 hour, 2 hours, 4 hours, and 24 hours after electroacupuncture. Photoplethysmography-derived PRV and radial pulse tonometry data will be recorded at baseline and after 2 hours under standardized resting conditions. The same schedule will be followed for visit 2 after the 7-day or longer washout period.

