### Outcome Measures

The primary outcomes are baseline-adjusted changes in pain intensity (11-point NRS; 0-10) at 15 minutes and 2 hours after each intervention. Change scores will be calculated as the postintervention NRS score at each specified time point minus the visit-specific preintervention baseline NRS score. The 15-minute time point was selected to evaluate immediate analgesic response after the 15-minute electroacupuncture stimulation, and the 2-hour time point was selected to evaluate whether the short-term analgesic response is maintained during the standardized in-clinic observation period.

Secondary outcomes will include pain NRS scores immediately after and at 1, 4, and 24 hours after electroacupuncture; pain location and quality; Photoplethysmography-derived PRV indexes (eg, total power, low frequency, high frequency, very low frequency, and low frequency–to–high frequency ratio); radial pulse tonometry parameters (eg, stroke volume, stroke volume index, cardiac output, systemic vascular resistance index, and waveform features); and physical activity metrics (steps, distance, and energy expenditure) from a wrist-worn device during the 2-hour in-clinic observation period.

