## Discussion

This randomized active-comparator crossover trial is expected to clarify whether short-term pain reduction differs between 2-Hz and 100-Hz electroacupuncture in patients with postoperative musculoskeletal pain. These results will directly inform the optimal frequency selection and outcome assessment timing for future definitive efficacy trials. The paired physiological measurements are expected to provide preliminary information on whether short-term analgesic responses are accompanied by changes in photoplethysmography-derived PRV and radial pulse tonometry parameters.

The rationale for comparing 2-Hz and 100-Hz electroacupuncture is based on frequency-dependent analgesic mechanisms. Low-frequency electroacupuncture (2 Hz) is expected to preferentially activate β-endorphin and enkephalin pathways with descending serotonergic and noradrenergic inhibition, whereas high-frequency electroacupuncture (100 Hz) is expected to engage dynorphin-mediated spinal antinociception [20]. We hypothesize that these distinct pathways will contribute to observable differences in both subjective pain relief and objective physiological measures. This protocol extends prior postoperative electroacupuncture research by using an intraindividual crossover design, a conservative washout period, and concurrent patient-reported and physiological measures to characterize short-term frequency-dependent responses.

The strengths of this trial include its randomized crossover design, within-participant comparison of 2 active electroacupuncture frequencies, standardized bilateral ST36 to SP9 stimulation, prespecified short-term outcome time points, and concurrent physiological measurements. The frequency-masked procedure, separation of the outcome assessor from the treating practitioner whenever feasible, and blinded statistical analysis are intended to reduce bias related to subjective pain assessment.

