Certain limitations should be considered. First, as an active-comparator trial lacking a sham or inactive control, this study is designed to compare frequency-dependent responses rather than evaluate the absolute efficacy of electroacupuncture or control for placebo effects. Second, although participants will not be informed of the assigned stimulation frequency, masking may be incomplete because sensory perceptions can differ between 2-Hz and 100-Hz stimulation. Third, this is a single-center study with a modest sample size, which limits generalizability and precludes meaningful subgroup analyses. Fourth, postoperative pain may change with the recovery phase; therefore, days since surgery will be recorded and considered in the analysis. Finally, PRV derived from photoplethysmography will be used as a surrogate for electrocardiogram-derived heart rate variability, and findings from PRV should be interpreted accordingly.

The findings will be used to estimate effect size and variability, refine outcome timing, and inform sample size calculations for a future definitive trial. Future studies should consider including sham, usual care, or no-additional-electroacupuncture control groups; assessor blinding where feasible; multicenter recruitment; and stratification by surgical procedure, pain phenotype, analgesic use, and postoperative recovery phase. The results of this trial will be disseminated through peer-reviewed publications and conference presentations.

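### A 1-minute pulse rate variability record cannot measure very low frequency power, which is a named secondary outcome, and gives imprecise total power, LF and LF/HF

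*Protocol article*

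**What the plan says.** The article's section Physiological Measurements and Activity Monitoring describes one finger-clip measurement per assessment: "an additional 2- to 3-minute stabilization period will be allowed before the 1-minute recording". The settling time precedes the record and is not part of it. On processing, the same section says: "The collected signals will be analyzed using the manufacturer-provided software according to predefined artifact handling and analysis procedures". Band limits and the spectral method are not given.

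Outcome Measures lists the PRV indexes, by way of example, as "total power, low frequency, high frequency, very low frequency" and the LF/HF ratio. The schedule provides two assessments per visit: "Photoplethysmography-derived PRV and radial pulse tonometry data will be recorded at baseline and after 2 hours under standardized resting conditions". No longer or repeated record is described, and no reason is given for the 1-minute length.

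The Discussion expects preliminary information on "whether short-term analgesic responses are accompanied by changes in photoplethysmography-derived PRV and radial pulse tonometry parameters". Its limitations paragraph covers PRV only as a surrogate for electrocardiogram-derived variability, ending "findings from PRV should be interpreted accordingly". Record length is not mentioned.

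**The concern.** Record length sets the slowest oscillation that a spectrum can resolve. VLF power is by definition the power in slow oscillations, with periods from about 25 s to several minutes under the usual limits. A 60 s record sees part of one such cycle, or at best two and a half. Total power contains VLF. LF begins only slightly above the point where the record runs out of cycles.

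At stake is the trial's physiological reading. A null VLF result could be read as no autonomic change, and a chance VLF or LF/HF difference as a mechanism, when the record could not support either statement. The findings are also meant to inform a later definitive trial, so an unsuitable index could be carried forward.

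**Working it through.** The article states no figure to reproduce here; the check compares the stated record length with the stated indexes.

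**Inputs**
- Record length T = 60 s (Physiological Measurements and Activity Monitoring).
- Indexes: total power, LF, HF, VLF, LF/HF (Outcome Measures).
- Two records per visit and two visits, so four per participant (schedule).
- 26 evaluable and 30 enrolled participants (Sample Size).
- Assumed, not in the article: VLF 0.0033-0.04 Hz, LF 0.04-0.15 Hz, HF 0.15-0.40 Hz.

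**Step 1: resolution and cycles.** Resolution = 1/T = 1/60 = 0.0167 Hz. Cycles in the record = frequency × T.

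| Band | Cycles in 60 s | Bins at 60 s | Bins at 300 s |
|---|---|---|---|
| VLF | 0.2-2.4 | 2 | 11 |
| LF | 2.4-9 | 6 | 33 |
| HF | 9-24 | 15 | 75 |

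The two VLF bins lie at 0.0167 and 0.0333 Hz. Moving the upper VLF limit to 0.05 Hz still leaves two bins below it. Oscillations slower than 0.0167 Hz never complete a cycle. They occupy (0.0167 − 0.0033)/(0.04 − 0.0033) = 36% of the band's width. If VLF power falls as 1/frequency, they carry ln(0.0167/0.0033)/ln(0.04/0.0033) = 1.62/2.49 = 65% of its power.

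**Step 2: illustrative simulation.** Stationary Gaussian series at 4 Hz with equal true VLF, LF and HF power (VLF shaped as 1/frequency, LF peak at 0.10 Hz, HF peak at 0.25 Hz), linear detrending, Hann window and periodogram; 1,800 records per length.

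| | 60 s: mean/truth | 60 s: CV | 300 s: mean/truth | 300 s: CV |
|---|---|---|---|---|
| VLF | 0.39 | 99% | 0.97 | 50% |
| LF | 1.00 | 67% | 1.00 | 31% |
| HF | 1.03 | 52% | 1.00 | 25% |
| Total power | 0.81 | 39% | 0.99 | 21% |

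The total power figure follows from its parts: (0.39 + 1.00 + 1.03)/3 = 0.81.

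**Step 3: LF/HF from one record.** The SD of log(LF/HF) from sampling error alone was 0.84 at 60 s and 0.40 at 300 s. The 95% range is exp(1.96 × SD): about ×/÷5.2 at 60 s and ×/÷2.2 at 300 s.

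**Step 4: the trial contrast.** The difference between two changes (2 hours minus baseline, 2 Hz against 100 Hz) uses four records, so its sampling SD is √4 × 0.84 = 1.68. The ratio detectable with 80% power at two-sided 5% is exp(2.80 × SD/√n).
- 60 s, n = 30: exp(2.80 × 1.68/√30) = 2.4-fold. With n = 26: 2.5-fold.
- 300 s, n = 30: SD = 2 × 0.40 = 0.80, giving exp(2.80 × 0.80/√30) = 1.5-fold.
- 60 s, n = 30, without subtracting the noisy baseline: SD = √2 × 0.84 = 1.19, giving 1.8-fold.

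Biological variability comes on top in every case.

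**The case against.** The strongest reply separates the indexes. A reader might infer that total power and LF/HF are as worthless as VLF, or that any PRV difference between frequencies would be uninterpretable. The documents and the arithmetic do not support that. In the simulation LF and HF are nearly unbiased and total power keeps about four fifths of its true value; their weakness is precision. The planned record length is the same at both assessments and under both frequencies, within a randomized within-participant comparison. Sampling error therefore costs power without creating a spurious frequency effect. This part stands and limits the point.

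A second reply is that the manufacturer's software follows predefined procedures that the article does not show. That matters for the percentages, which depend on band limits, spectrum shape and method. It does not rescue VLF, because software cannot restore cycles that were never recorded.

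A third is that PRV is secondary, its indexes are given as examples, and the Discussion promises only preliminary information. This is true and bounds the consequence. It does not remove the mismatch between a named outcome and its measurement.

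A reader might also conclude that records should now be lengthened. By June 8, 2026, all 30 participants had been recruited, so remaining visits are probably mostly second visits. A change there would mix record lengths within participants and confound length with period. Deleting LF as well would go further than its near-unbiasedness justifies and, this late, would invite a charge of selective reporting.

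**Conclusion.** The point holds in graded form.

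- **VLF:** not measurable from 60 s. The cycle and bin counts settle this and depend only on the assumed band limits.
- **Total power:** inherits part of the VLF loss (about 81% recovered). The exact share depends on the assumed spectrum and method.
- **LF and LF/HF:** computable but imprecise (×/÷5.2 for one LF/HF record), so only a roughly 1.8- to 2.5-fold frequency difference would be reliably detected, before biological variability.
- **HF:** the least affected spectral index, though its single-record CV was still 52%.

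The shortfall lowers sensitivity and does not by itself bias the 2-Hz versus 100-Hz comparison. The stronger conclusion, that every PRV difference would be meaningless, is not supported. The primary NRS outcomes and the sample size are untouched.

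**What to change.** Before database finalization and analysis, planned for late 2026:

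1. Remove VLF from the PRV outcomes, or keep it and report it as not interpretable from a 1-minute record. Keeping it with that label best avoids any appearance of selective reporting.
2. Label total power, LF and LF/HF as exploratory with low precision.
3. Base any statement on autonomic change on HF power and on mean pulse rate or beat-to-beat time-domain measures. The article's example list does not name the last two, so they should be specified before the data are examined.
4. Add record length to the limitations paragraph of the Discussion, beside the surrogate caveat.
5. Leave the record length unchanged for the remaining visits, and plan a longer record in the future trial.

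The cost is wording, plus a formal IRB amendment where the change counts as a protocol modification under Ethical Considerations. The downside is that fewer PRV indexes can support a conclusion.
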